### Sample size calculation

2.7

Sample size for this study is estimated according to the formula for the comparison of means in a randomized controlled trial. Referring to the relevant literatures (26, 27), we estimate the pooled standard deviation (*σ*) of the treatment group and the control group to be 7.81, and the difference between the means of the two groups (*δ*) to be 6.59. We set the significant level (*α*) at 0.05, the Type II error rate (*β*) at 0.1, and the statistical power (1-β) at 0.9. After substituting the values into the formula, calculated sample size per group requires 30 cases. Considering a 15% dropout rate, a total of 70 cases will be enrolled.

$$n=\frac{2{\left(z_{\alpha }+z_{\beta }\right)}^{2}*\sigma^{2}}{\delta^{2}}$$

### Randomization and allocation concealment

2.8

The grouping will be performed using a completely random method. The random allocation sequence will be generated through an online randomization tool Med Sci (http://tools.medsci.cn/rand) and managed by an independent researcher. Stroke patients who meet the inclusion criteria will be randomized into the acupuncture group or the sham acupuncture group in a 1:1 ratio after signing the informed consent. Cards printed with information on the allocated groups will be placed in opaque envelopes. Patients will receive envelopes sequentially according to the order of inclusion. An acupuncturist will open envelopes prior to treatment and conduct the corresponding treatment. The randomization process will be carried out by an independent researcher who is not involved in the recruitment, evaluation, and intervention.

### Blinding

2.9

This study will employ blinding in efficacy assessment and statistical analysis. Since sham acupuncture will be used as the control, it is difficult to blind participants and acupuncturists. Additionally, the grouping information will be blinded to efficacy assessors and statistical analysts. Acupuncturists will administer acupuncture therapy in accordance with the treatment plans corresponding to the random numbers. Patients will be separated to prevent communication. Researchers responsible for scale evaluation and EEG analysis will not participate in the grouping or intervention processes. Besides, statistical analyst will not be involved in the implementation of the study to avoid selective bias produced by objective factors.

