#### Sham acupuncture treatment

2.10.3

The sham acupuncture method will be employed as a parallel control for the acupuncture treatment group. The operation of the sham acupuncture will be defined by three elements (29): (1) the acupuncture points are located 1 cun lateral to the reference acupoints at the horizontal level, and needling these positions will not affect the therapeutic efficacy for stroke; (2) superficial insertion (depth of 1–3 mm); (3) no manipulation after needle insertion to avoid achieving the *De qi* sensation (Figure 3). A rubber pad will be placed on the skin of corresponding acupuncture sites of the two groups to alleviate patients’ fear of needling. Importantly, it simulates the sensation of real acupuncture manipulation, keeping the needle upright on the skin without actual skin penetration in the sham acupuncture group. Patients in the sham acupuncture group will receive 2 weeks of compensatory acupuncture treatment after the observation period.

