
There are still some limitations in the design of this study: (1) the study does not restrict the infarction sites of included patients to the same hemisphere or specific locations, leading to increased heterogeneity in EEG signals; (2) the study duration is short, and there is a lack of follow-up observation after treatment course, making it difficult to ascertain the long-term efficacy of acupuncture therapy; (3) due to the treatment characteristics of acupuncture, it is challenging to implement blinding for acupuncturists and patients; (4) a multicenter study is not designed, making it impossible to verify the general applicability of the study across different populations and medical conditions. Hence, based on this study, we will further conduct multicenter, large-sample, long-term follow-up clinical trials for ischemic stroke patients in recovery stage.

Collectively, the primary objective of this clinical trial is to evaluate the efficacy and safety of the “simultaneous treatment of phlegm and blood stasis” acupuncture therapy in improving limb motor impairment in ischemic stroke patients with hemiplegia using functional scales, while exploring its underlying electrophysiological mechanisms through EEG. By conducting this clinical study, we expect to provide reliable scientific evidence for the clinical application of acupuncture therapy featuring characteristic acupoint combinations based on TCM syndrome differentiation in the field of neurological rehabilitation for ischemic stroke.

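### Participant blinding is set aside because a sham is used, although the sham is built to mask; performance-based outcomes are left at avoidable risk of expectation bias

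*Protocol article*

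**What the plan says.** **Who is blinded.** Section 2.9 (Blinding) opens with "This study will employ blinding in efficacy assessment and statistical analysis" and specifies that "the grouping information will be blinded to efficacy assessors and statistical analysts". The title, abstract and section 2.1 claim the same two roles and no more. On participants, 2.9 says "Since sham acupuncture will be used as the control, it is difficult to blind participants and acupuncturists". The third limitation in the Discussion repeats that "it is challenging to implement blinding for acupuncturists and patients", there attributing it to the nature of acupuncture as a treatment.

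**Features that serve masking.** Section 2.10.3 (Sham acupuncture treatment) states "A rubber pad will be placed on the skin of corresponding acupuncture sites of the two groups", first to ease fear of needling, and adds that in the sham arm "it simulates the sensation of real acupuncture manipulation". Section 2.9 adds "Patients will be separated to prevent communication".

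**Handling of the allocation.** In section 2.8 the group is printed on a card inside an opaque envelope, and "Patients will receive envelopes sequentially according to the order of inclusion". An acupuncturist then opens the envelope before treatment.

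**Other relevant text.** Only the sham group is promised compensatory acupuncture after observation ends (2.10.3), and this is also listed as a compliance measure (2.15). The primary outcome is change in limb motor function on the simplified FMA (2.12.1). BBS items are scored on what the patient does (2.12.2.1). Every patient has individually set rehabilitation of about one hour, five times a week for two weeks (2.10.1).

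**The concern.** A sham control is mainly there to keep patients from knowing which treatment they receive, so that the contrast isolates needling from expectation. Giving the sham as the reason that patients are hard to blind turns this round. The plan pays for a masking device and then makes no commitment to use it: no sentence says the arm is to be kept from patients.

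Blinded assessors guard against biased scoring. They do not guard against changed behaviour by the patient. Someone who knows they are on sham may put less into the motor and balance tests or into daily rehabilitation, may withdraw, or may tell the assessor. The primary comparison would then mix the effect of needling with the effect of knowing one's arm, and no analysis can separate the two afterwards.

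**Working it through.** **1. The passages side by side**

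| Question | Where | What the text supports |
|---|---|---|
| Is participant blinding claimed? | Title, 2.1, 2.9 | No; assessors and statisticians only |
| Reason given | 2.9 | A sham is used |
| Reason given | Discussion, limitation 3 | Nature of acupuncture |
| Is a masking device present? | 2.10.3 | Yes, pads in both groups, imitating real needling |
| Are patients kept from comparing notes? | 2.9 | Yes, they are separated |
| Must the arm be withheld from patients? | Nowhere | Not stated |
| Who receives the envelope? | 2.8 | The patient |
| Who opens it? | 2.8 | The acupuncturist |

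The reason in 2.9 holds for acupuncturists, who must know which procedure to perform. It does not hold for participants, and it conflicts with the pads and the separation.

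Section 2.10.3 also describes the sham needle both as inserted superficially, 1–3 mm, and as not penetrating the skin. These statements conflict and must be reconciled, because what the patient feels bears on whether masking can work.

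**2. The plan's own figure** (section 2.7: δ = 6.59, σ = 7.81, α = 0.05, power 0.9; two-sided testing from 2.16)

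n = 2(z₀.₉₇₅ + z₀.₉₀)² σ²/δ² = 2(1.960 + 1.282)² × 7.81²/6.59² = 29.52, rounded up to 30 per group. The stated figure reproduces, and the point about blinding does not depend on it.

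**3. Illustration of what a bias would do**

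The documents give no size for expectation bias. The values of b below are assumptions, in FMA points favouring acupuncture, with no true effect of needling.

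- SE of the difference = σ√(2/n) = 7.81 × √(2/30) = 2.017.
- Degrees of freedom = 58; two-sided 5% critical value = 2.002.
- Non-centrality = b/2.017; false-positive rate = P(|T| > 2.002) under the non-central t distribution.

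| Assumed bias b | b as share of 6.59 | Non-centrality | False-positive rate |
|---|---|---|---|
| 0 | 0% | 0 | 5.0% |
| 0.5 | 8% | 0.248 | 5.7% |
| 1 | 15% | 0.496 | 7.8% |
| 2 | 30% | 0.992 | 16.4% |
| 3 | 46% | 1.488 | 31.0% |

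A normal approximation gives 5.7%, 7.9%, 16.8% and 31.9% for the last four rows; the small gap is the method. The calculation takes 30 analysed patients per group and an unadjusted comparison. The ANCOVA planned in 2.16 would change the SE, so the rates are indicative only.

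**The case against.** **The lack of participant blinding is disclosed.** The title claims only assessor and statistician blinding, and the Discussion lists patient blinding as a limitation. No reader is misled about who is blinded. That stands, but disclosure does not resolve the conflict between 2.9 and 2.10.3 or remove the part of the risk that is avoidable.

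**Masking may fail anyway.** Real needles are manipulated until De qi is reached, while the sham is left unmanipulated to avoid it. Patients may tell the difference. This stands as a limit on what masking can achieve, but not as a reason to leave it uncommitted.

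**The sham is not wasted.** Even unmasked, it equalises session time, practitioner contact and ritual. This is right.

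**Stronger readings that the text does not support.**

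- A reader might infer from 2.8 that patients learn their arm from the envelope. It is opaque and the acupuncturist opens it; nothing says the patient reads the card.
- A reader might infer that patients are told their arm. The text calls blinding difficult and says neither that they are told nor that they are not.
- A reader might infer that the outcomes are biased. Only a risk can be shown, and the figures above have no anchor in the documents: they show how the test reacts to a bias, not how large it is here.
- A reader might fault the consent wording or assume that rehabilitation therapists know the arm. The consent form is not shown, and the article is silent on the therapists.

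**Conclusion.** The concern holds as an internal contradiction with a practical consequence. Section 2.9 gives a reason that does not apply to participants, the sham in 2.10.3 is equipped to mask them, and nothing obliges anyone to keep the arm from them. FMA, BBS and engagement in rehabilitation are at avoidable risk of expectation bias that assessor blinding does not cover.

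The size is unknown. On the planning SD with 30 per group, an assumed bias of 1 to 3 FMA points would lift the two-sided false-positive rate from 5% to about 8% to 31%; at 0.5 points the effect is slight (5.7%). The conclusion rests on the text, not on these figures. Severity: should-fix, as a cheap improvement. Assessors and analysts are blinded and the limitation is disclosed, so it falls short of a fatal defect.

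**What to change.** - **Section 2.9:** state that participants are not told their arm until their Day 15 assessments are complete. Correct the stated reason, so that only the acupuncturist is necessarily unblinded.
- **Section 2.8:** have the independent researcher give the envelope directly to the acupuncturist, who does not disclose its content.
- **Sections 2.10.3 and 2.15:** tell individual patients about their own compensatory sessions only after Day 15, since an earlier offer would reveal the arm.
- **Section 2.10.3:** reconcile the two descriptions of the sham needle, superficial insertion and no skin penetration.
- **Day 15 case report form:** add one treatment-guess question and report it by arm, so that readers can judge how well masking worked.

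Patient information must stay consistent with the commitment in section 2.2 to inform patients fully; withholding the individual allocation does not require hiding that one arm is a sham.

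The cost is protocol wording, one form item and an ethics amendment. Because the trial is already recruiting, the date of the change should be recorded so that patients treated before and after it can be identified. Masking may still be imperfect because De qi differs between arms; the treatment-guess result would help to show how far.

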### Intervention

2.10

#### Conventional treatment

2.10.1

Eligible patients will be randomized into the acupuncture group or sham acupuncture group for a two-week treatment. During the study period, all patients will receive Western medicine treatment following “Chinese Guidelines for Diagnosis and Treatment of Acute Ischemic Stroke 2023” (23), including anti-platelet aggregation, improving cerebral circulation, reducing blood pressure, lowering blood glucose, lowering lipid, etc. Simultaneously, patients will undergo routine rehabilitation treatment in accordance with the “China Guidelines for Stroke Rehabilitation” (28), which includes physical therapy treatments, such as proper limb positioning, joint range-of-motion training, muscle strengthening training, balance and coordination training, standing training, and gait training, as well as occupational therapy, involving fine motor training and activities of daily living training. The rehabilitation programs will be set based on individual conditions and carried out five times per week for 2 weeks, and each rehabilitation treatment session will last for approximately 1 h.

#### Acupuncture treatment

2.10.2

Based on previous treatment experience, the acupuncturists will select combined acupoints on the affected side of stroke patients, guided by the TCM theory of “simultaneous treatment of phlegm and blood stasis,” which include Jianyu (LI15), Quchi (LI11), Hegu (LI4), Waiguan (SJ5), Zusanli (ST36), Fenglong (ST40), Xuehai (SP10), Sanyinjiao (SP6), and Xuanzhong (GB39). The acupoint location conforms to “nomenclature and location of meridian points” (GB/T12346-2021) issued in 2021. Acupuncture therapy will be administered by a licensed acupuncturist with over 5 years of experience, who has undergone uniform training prior to the onset of the study. The patients will take the supine position, fully exposing acupuncture site. After disinfection with 75% medical alcohol, the acupuncturist will employ disposable sterile stainless-steel needles (0.25 × 40 mm, Huatuo, Suzhou, China) for the treatment. According to different acupoints, the acupuncturist will insert needles vertically and manipulate them in turn by twirling, lifting, and thrusting for 1 min until the *De qi* sensation is achieved (a compositional sensation including soreness, numbness, distention, and heaviness). After that, the needle will be retained for 30 min. The localization of the acupoints is presented in Table 2 and Figure 2. The treatment will be administered for 5 consecutive days from Monday to Friday, followed by a 2-day weekend, making it a 10-day treatment course in total, and the duration of each session will be 30 min. The temperature in the treatment room remain above 25°C during the treatment for ensuring patients’ comfort and safety.

**Table 2 tab2:** Location of acupoints.

Acupoints	Meridians	Locations	Insert angle	Insert depth
Jianyu (LI15)	Large Intestine Meridian of Hand-Yangming	At the inferior border of the acromial end of the clavicle, between the acromion and the greater tuberosity of the humerus, in the central upper part of the deltoid	90°	1 cun
Quchi (LI11)	Large Intestine Meridian of Hand-Yangming	With the elbow flexed to 90°, at the midpoint of the line connecting the lateral border of the elbow flexion crease and the lateral epicondyle of the humerus	90°	1 cun
Hegu (LI4)	Large Intestine Meridian of Hand-Yangming	At the midpoint on the radial side of the 2^nd^ metacarpal bone between the 1^st^ and 2^nd^ metacarpals	90°	1 cun
Waiguan (SJ5)	Sanjiao Meridian of Hand-Shaoyang	At 2 cun proximal to the distal wrist crease, on the midpoint of the line connecting the ulna and radius	90°	1 cun
Zusanli (ST36)	Stomach Meridian of Foot-Yangming	At 3 cun distal to Dubi (ST35) along the line connecting Dubi and Jiexi (ST41), one finger-breadth lateral to the anterior border of the tibia	90°	1.5 cun
Fenglong (ST40)	Stomach Meridian of Foot-Yangming	At 8 cun superior to the tip of the lateral malleolus, and two finger-breadths lateral to the anterior crest of the tebia	90°	1.5 cun
Xuehai (SP10)	Spleen Meridian of Foot-Taiyin	Flex knee 90°, at 2 cun above the medial end of the patella’s top edge, at the peak of the inner thigh muscle bulge	90°	1 cun
Sanyinjiao (SP6)	Spleen Meridian of Foot-Taiyin	At 3 cun above the medial malleolus apex, along the posterior depression adjacent to the tibial medial border	90°	1 cun
Xuanzhong (GB39)	Gallbladder Meridian of Foot-Shaoyang	At 3 cun above the lateral melleolus apex, along the anterior border of the fibula	90°	1 cun

**Figure 2 fig2:**
[figure not shown]
Location of acupoints.

#### Sham acupuncture treatment

2.10.3

The sham acupuncture method will be employed as a parallel control for the acupuncture treatment group. The operation of the sham acupuncture will be defined by three elements (29): (1) the acupuncture points are located 1 cun lateral to the reference acupoints at the horizontal level, and needling these positions will not affect the therapeutic efficacy for stroke; (2) superficial insertion (depth of 1–3 mm); (3) no manipulation after needle insertion to avoid achieving the *De qi* sensation (Figure 3). A rubber pad will be placed on the skin of corresponding acupuncture sites of the two groups to alleviate patients’ fear of needling. Importantly, it simulates the sensation of real acupuncture manipulation, keeping the needle upright on the skin without actual skin penetration in the sham acupuncture group. Patients in the sham acupuncture group will receive 2 weeks of compensatory acupuncture treatment after the observation period.

**Figure 3 fig3:**
[figure not shown]
Diagram of the acupuncture and sham acupuncture.

### Basic information collection

2.11

Basic demographic and medical history data from eligible patients will be collected using a self-designed questionnaire, including gender, age, education, marital status, residence, occupation, as well as smoking/alcohol use, family stroke history, underlying diseases, and medication history. Basic information and baseline assessments will be recorded and gathered post random grouping.

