### Study design

2.1

This is a single-center, assessor-and-statistician-blinded, randomized, sham acupuncture-controlled clinical trial. The study aims to evaluate the efficacy and safety of acupuncture therapy, featuring acupoint combination for “simultaneous treatment of phlegm and blood stasis,” in treating ischemic stroke patients with hemiplegia. The study has been registered on itmctr.ccebtcm.org.cn (Registration No. ITMCTR2025001171). SPIRIT checklist is shown in Supplementary file 1.

The study will recruit 70 eligible ischemic stroke patients with unilateral limb dysfunction who meet the inclusion criteria. After signing informed consent, the participants will be randomized into acupuncture group or sham acupuncture group in a 1:1 ratio. All participants will receive a two-week treatment. Basic information will be collected before treatment (Day −1 to 0), and electroencephalogram (EEG) examination and scale evaluation will be conducted before (Day −1 to 0) and after the two-week treatment (Day 15). Allocation information will be confidential to assessors. The study process is shown in Figure 1 and the timeline for enrolment, intervention and assessment is shown in Table 1. The study will be started in June 2025 and complete recruitment by June 2028. The entire study is expected to be finalized by December 2028.

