#### Primary outcome

2.12.1

The primary outcome is the change in limb motor function in stroke patients before and after treatment, assessed using the simplified Fugl-Meyer Assessment (FMA) scale. Limb motor function impairment will be quantified by evaluating upper/lower extremity functions, balance, sensation, and joint range of motion. The scale comprises 50 items (33 for upper limbs, 17 for lower limbs), with higher scores indicating better functional activity.

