### Statistical analysis

2.16

All data will be analyzed using SPSS 27.0 statistical software. In accordance with the intention-to-treat (ITT) principle, patients who have received at least one treatment session will be included in the analysis. Basic information, baseline data, and efficacy evaluation will be analyzed using both the full analysis set (FAS) and per-protocol set (PPS). In case of inconsistent results between the two datasets, further analysis and evaluation will be conducted. Missing data will be imputed using multiple imputation method. For continuous outcomes, post-treatment data are presented as mean±SD if normally distributed with equal variances; otherwise, they are presented as median (IQR). ANCOVA will be used to adjust for baseline values and confounders (e.g., age, gender, revascularization therapy status), with adjusted mean differences and 95% CIs reported. For categorical data, frequencies and percentages will be presented, and potential confounders will be screened via univariate analysis before constructing stepwise logistic regression models to adjust for confounders and report odds ratios with 95% CIs, followed by validation of the model’s goodness of fit. Further, patients will be grouped based on infarction location to analyze EEG indicators in each subgroup. Receiver operating characteristic (ROC) curve analysis will be conducted to evaluate the predictive value of EEG as an efficacy indicator for acupuncture response, with the area under the curve (AUC) and 95% CI reported. For correlation analysis, Pearson correlation will be applied to normally distributed continuous data, while Spearman correlation will be used for ordinal data. All data analysis will be conducted using two-tailed tests with a significant level of 5%.

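### Section 2.11 gathers baseline after randomisation and nothing keeps the envelope sealed until baseline is complete, so knowledge of the arm could affect the baseline FMA

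*Protocol article*

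**What the plan says.** Section 2.11 (Basic information collection) fixes the order: "Basic information and baseline assessments will be recorded and gathered post random grouping".

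The other relevant sections are:

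- **Section 2.1 (Study design)** times the assessments against treatment, not against randomisation: "scale evaluation will be conducted before (Day −1 to 0) and after the two-week treatment (Day 15").
- **Table 1** lists consent, randomisation, allocation and all baseline scales and EEG in a single pre-treatment column, so it gives no order among them.
- **Section 2.8 (Randomization and allocation concealment)** randomises after consent and does not require baseline first. It says "Patients will receive envelopes sequentially according to the order of inclusion". The envelopes are opaque, and the acupuncturist opens them at some point before treatment.
- **Section 2.9 (Blinding)** says "Since sham acupuncture will be used as the control, it is difficult to blind participants and acupuncturists", while "the grouping information will be blinded to efficacy assessors and statistical analysts". The limitations in section 3 repeat that blinding patients and acupuncturists is a challenge.
- **Section 2.12.1 (Primary outcome)**: "The primary outcome is the change in limb motor function in stroke patients before and after treatment", measured on the simplified FMA.
- **Section 2.16 (Statistical analysis)**: "ANCOVA will be used to adjust for baseline values and confounders".

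**The concern.** A change from baseline and a baseline-adjusted comparison are both protected by randomisation only if assignment cannot affect the baseline. The usual safeguard is to finish baseline before the allocation exists, or at least before anyone involved can learn it. Section 2.11 states the opposite order, and no other section supplies the safeguard by keeping the envelope closed.

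This matters more here than in a fully blinded trial. The plan does not count on participants being blind. The FMA is a performance test that depends in part on effort, and the TCM syndrome score (section 2.12.2.5) includes clinical symptoms. A patient who learned the arm before being assessed could perform or report differently. The baseline FMA is used both in the primary change score and as the covariate, so an arm-related shift would pass into the primary estimate. The secondary scales and EEG follow the same timetable.

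**Working it through.** **1. Does any section put baseline before randomisation?**

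| Place | What it fixes | Baseline before randomisation? | Envelope sealed until baseline done? |
|---|---|---|---|
| 2.11 | Baseline follows grouping | No, the reverse | Not stated |
| 2.1 | Baseline on Day -1 to 0, before treatment | Not stated | Not stated |
| Table 1 | One pre-treatment column | Not stated | Not stated |
| 2.8 | Randomisation after consent; envelope opened before treatment | Not stated | Not stated |

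These entries are compatible with each other. Section 2.11 is the only statement on order. Envelope opening and baseline assessment may both fall in the pre-treatment window, in either sequence.

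**2. The plan's own figure (section 2.7).** Inputs: SD 7.81, difference 6.59, alpha 0.05 two-sided (section 2.16), power 0.9.

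n = 2 x (1.960 + 1.282)^2 x 7.81^2 / 6.59^2 = 29.52, so 30 per group.

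The stated 30 reproduces. The order of procedures does not alter it. The 6.59 serves below only as a yardstick.

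**3. How a baseline shift enters the estimate.** The ANCOVA estimate is

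adjusted difference = (Day 15 mean, acupuncture - Day 15 mean, sham) - b x (baseline mean, acupuncture - baseline mean, sham),

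where b is the slope of Day 15 on baseline. If knowledge of the arm moves the recorded baseline in the acupuncture arm by s relative to sham, and Day 15 is unaffected, then

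bias = -b x s.

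For an unadjusted change score, b = 1 and the bias is -s. The sign matters. Extra effort at baseline by patients who know they will receive acupuncture (s > 0) would understate the effect. Extra effort by patients who know they will receive sham (s < 0) would overstate it.

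**4. Illustration on assumed values.** The documents give neither b nor s. The calculation assumes 30 per arm and treats 7.81 as the residual SD, so the standard error is 7.81 x sqrt(2/30) = 2.02.

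| Assumed absolute shift s | Assumed slope b | Absolute bias | Share of 6.59 | Two-sided type I error |
|---|---|---|---|---|
| 0 (sealed until baseline done) | any | 0 | 0% | 0.050 |
| 0.5 | 0.5 to 1.0 | 0.25 to 0.5 | 4% to 8% | 0.052 to 0.057 |
| 1 | 0.5 to 1.0 | 0.5 to 1.0 | 8% to 15% | 0.057 to 0.079 |
| 2 | 0.5 to 1.0 | 1.0 to 2.0 | 15% to 30% | 0.079 to 0.168 |

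If the bias runs against acupuncture, power at 30 per arm falls from 0.905 with no bias to 0.624 at the largest value shown (2.0 points).

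**The case against.** The strongest reply is that random grouping may mean only that a sealed number has been assigned. The envelopes are opaque, the acupuncturist opens them, and no needling has taken place before Day 1 from which a patient could guess the arm. If the envelope stays closed until baseline is done, neither patient nor assessor knows the arm and the bias is zero. This reply stands as a possible reading. However, the protocol does not state the condition on which it depends.

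Several stronger readings are tempting, and the documents do not support them.

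- **That patients know their arm at baseline.** Section 2.8 has patients receive envelopes, but the acupuncturist opens them. Section 2.9 calls participant blinding difficult and does not say that patients are told. Rubber pads in both groups (section 2.10.3) and separation of patients (section 2.9) are meant to limit guessing. Knowledge at baseline is possible, not shown.
- **That only the Day 15 assessor is blinded.** Section 2.9 sets no such limit, so assessor-driven distortion of baseline is already addressed. Only a patient-driven shift remains.
- **That a bias of a given size is to be expected.** The shift and slope are assumed, the range includes zero, and the direction is unknown.
- **That patients lost between grouping and baseline leave gaps in the analysis.** Baseline precedes treatment, and section 2.16 analyses patients with at least one session. Someone who leaves before baseline is outside that set anyway.

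A statistical analysis plan or fuller protocol may exist. That does not answer the point, because section 2.11 is an explicit instruction and not an omitted detail.

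**Conclusion.** The point holds as a risk in the stated order of procedures. Baseline is placed after randomisation, no section keeps the allocation hidden until baseline is complete, and the exposed measurement feeds the primary change score and the ANCOVA. Assessor blinding reduces the risk but cannot remove a shift produced by the patient.

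The size is unknown. It is zero if envelopes stay sealed until baseline is finished. Purely as illustration, it reaches about 2 FMA points in absolute value (2.0/6.59 = 30%) with an assumed slope of 1.0 and shift of 2, in either direction. These figures rest on assumed inputs and on judging FMA performance to be partly effort-dependent. They should not be read as an estimate of actual bias. The planned sample size is unaffected. This should be fixed, but it does not show that the trial's result is compromised.

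**What to change.** Replace the sentence in section 2.11 with wording to this effect:

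> All baseline data, scales and EEG are completed and locked by the blinded assessor after consent and before the allocation is assigned; at minimum, the envelope remains sealed until baseline is locked.

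Align section 2.8 with this, and divide the first column of Table 1 to show consent, then baseline, then randomisation. Record the date and time of baseline completion, of allocation and of envelope opening for every patient.

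The cost is small. The steps already share the Day -1 to 0 window, so no visit, test or staff is added and the total stays at 70. There is one downside. Section 4 says the trial is recruiting, so the change is prospective only. It must be reported to the Ethics Committee under section 2.17. The order actually used for patients already enrolled should be documented, because their baseline cannot be taken again once treatment has begun.
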